### Justification of dose

Initial drug dosing, dose modifications and management of drug-related toxicities will be according to the U.S. Food and Drug Administration (FDA) and/or European Medicines Agency (EMA) approved label (or under revision for approval) and/or manufacturer’s recommendations. If several doses are described, considerations will be made by the study team to select dosing based on current knowledge. Details on mechanism of action, potential risks and benefits, and considerations on concomitant medication are included in the protocol or the drug specific manuals with reference to the specific SmPC/IB.

### Patient selection and procedures

Patients with advanced malignancies are eligible after disease progression on standard treatment. Two informed consents are obtained, first for the molecular screening and, if the patient is eligible for treatment phase, the second drug specific consent for the specific drug available in the study for that molecular subgroup. Children are currently only eligible for the molecular screening.

The treating physician will determine whether a patient eligible for comprehensive molecular profiling meets all the general inclusion criteria and none of the exclusion criteria for participation in the molecular profiling phase and collect the first informed consent form (molecular profiling ICF). Two Norwegian university hospitals have established comprehensive molecular profiling—and the remaining four university hospitals are underway with establishing such diagnostics. This as part of the publicly funded Infrastructure for Precision Diagnostics—cancer (InPreD Norway). The comprehensive molecular profiling includes genomic analyses using the TruSight Oncology 500 panel (TSO500) by Illumina as the initial standard (now reimbursed as part of the health care in Norway) which can be supplemented with immunohistochemistry (IHC), fluorescence in situ hybridisation (FISH) or necessary molecular/diagnostic tests. The treating physician will submit a biopsy specimen for molecular profiling through their local pathology department according to guidelines. In addition, a plasma sample for trial-specific molecular testing (i.e. liquid biopsy) will be submitted to an approved trial laboratory. In January 2022, two of the university hospitals are approved trial laboratories, and the remaining university hospitals are planned ready within the next six months. If no tumour material is available, a patient can be included based on the liquid biopsy analysis alone. All study specific procedures must take place after signing the ICF. Plasma samples will also be collected and analysed for molecular alterations in ctDNA. The test results will be submitted to the national molecular tumour board and discussed together with the clinical data provided by the treating physician. The national molecular tumour board can advise on experimental treatment opportunities (i.e. available trials and compassionate use programs) including IMPRESS-Norway cohort inclusion. If one or more molecular variant fulfils the criteria defined for an available drug, the national molecular tumour board will advise a possible treatment in an IMPRESS-Norway cohort, as described below. If all drug specific eligibility criteria are confirmed, the patient can consent to treatment with the proposed drug and sign the drug-specific informed consent (see also Fig. 1 ‘Schematic overview of patient submission’). If an ongoing clinical study other than IMPRESS-Norway is available for the patient, recommendations for the patient will be made based on what may benefit the patient most.

**Fig. 1 Fig1:**
[figure not shown]
Flow chart of patient inclusion. Patients sign informed consent prior to the molecular screening. If offered treatment in a cohort, the patients sign a drug specific informed consent before initiating treatment

### Selected inclusion and exclusion criteria—molecular diagnostics screening phase

Selected inclusion criteriaECOG performance status 0–2.Patients must have measurable or evaluable disease. RECIST v1.1 [22, 23] will be used for patients with solid tumours. For patients with multiple myeloma or non-Hodgkin lymphoma, International Myeloma Working Group (IMWG) response criteria [24] and CHESON/Lugano guidelines [25] will be used, respectively. For glioblastoma patients, Response Assessment in Neuro-Oncology (RANO) criteria will be used [26]. iRECIST will be used for immunotherapy-cohorts. European LeukemiaNet recommendations for diagnosis and management of acute myeloid leukaemia (ELN-AML) response criteria will be used accordingly.Patients whose disease cannot be objectively measured by physical or radiographic examination (e.g., elevated serum tumour marker only) are NOT eligible, except for cancer antigen-125 (CA-125) for ovarian cancer and prostate-specific antigen (PSA) for prostate cancer [27].The patient is, in the opinion of the investigator, a candidate for a treatment cohort in IMPRESS Norway or another clinical study in NorwayAbility to understand and the willingness to sign a written informed consent

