## Methods/design

Oslo University Hospital is the sponsor of the study. All hospitals in Norway with an oncology or haematology care unit participate; recruiting patients for molecular profiling and providing study-specific treatment to patients included in a study cohort. Patient recruitment started in April 2021, and by March 7, 2022, 298 patients have been enrolled.

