### Selected inclusion criteria—treatment phase

To enter the treatment phase of the trial, both the above and the following criteria must apply; other drug specific criteria may be added in the Drug Specific Amendment.Patient with a pathology-proven non-curable malignant disease who is no longer benefitting from standard treatment or for whom, in the opinion of the investigator, no such treatment is available or indicated.Patients must have acceptable organ function as defined below (some specifics for hematologic diagnoses):Absolute neutrophil count ≥ 1.5 × 10^9^ /LHemoglobin ≥ 9 g/dlPlatelets ≥ 75,000/µlTotal bilirubin < 1.5 × institutional upper limit of normal (ULN)Aspartate aminotransferase (AST) (serum glutamic-oxaloacetic transaminase [SGOT]) and alanine aminotransferase (ALT) (serum glutamic-pyruvic transaminase < 2.5 × institutional upper limit of normal (ULN) (or < 5 × ULN in patients with known hepatic metastases)Calculated or measured creatinine clearance ≥ 40 mL/min/1.73 m^2^For orally administered drugs, the patient must be able to swallow and tolerate oral medication and must have no known malabsorption syndrome.Results must be available from a genomic / molecular test performed in a preapproved laboratory. The test used to qualify a patient for participation in IMPRESS-Norway may have been performed on any specimen of the patient’s tumour obtained at any point during the patient’s care at the discretion of the patient’s treating physician. Genomic assays performed on cell-free DNA in plasma (“liquid biopsies”) will also be acceptable. Information from these analyses might be used upon progression, for evaluation of possible new cohort-inclusion.Have a genomic profile indicating that treatment with one of the anti-cancer therapies included in this study may have potential clinical benefitWomen of child-bearing potential and men must agree to use adequate highly effective methods of contraception for the duration of study participationFemale participants must have a negative highly sensitive pregnancy test < 1 month prior to inclusion.Male patients should avoid impregnating a female partner.Ability to understand and the willingness to sign a written informed consent

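### As printed, the measurability criterion bars AML and myeloma patients who have no disease measurable by examination or imaging, although the same criterion names response scales for both diseases

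*Protocol article*

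**What the plan says.** All references are to the protocol article.

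The section on selected criteria for the molecular diagnostics screening phase opens broadly: "Patients must have measurable or evaluable disease". It then allocates response scales by disease: RECIST v1.1 for solid tumours, RANO for glioblastoma, iRECIST for immunotherapy cohorts, and scales for three haematological diseases. For two of these it says "For patients with multiple myeloma or non-Hodgkin lymphoma, International Myeloma Working Group (IMWG) response criteria", with CHESON/Lugano for the lymphomas. For the third it says "management of acute myeloid leukaemia (ELN-AML) response criteria will be used accordingly".

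The exclusion comes next: "Patients whose disease cannot be objectively measured by physical or radiographic examination (e.g., elevated serum tumour marker only) are NOT eligible", followed by its exceptions, "except for cancer antigen-125 (CA-125) for ovarian cancer and prostate-specific antigen (PSA) for prostate cancer". No other exception is printed.

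The section on selected inclusion criteria for the treatment phase imports these conditions: "To enter the treatment phase of the trial, both the above and the following criteria must apply". That section also provides for blood cancers: "Patients must have acceptable organ function as defined below (some specifics for hematologic diagnoses". Under Methods/design, "All hospitals in Norway with an oncology or haematology care unit participate". The section on the national molecular tumour board lists haematology among its fields of expertise.

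**The concern.** One criterion gives two answers for the same patient. Its first part provides a way to score response in myeloma and AML. Its second part makes measurement by examination or imaging a condition of entry and excepts only two solid-tumour markers. A myeloma patient followed only by a protein in serum comes close to the sentence's own example of who is ineligible.

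What is at stake is consistent application. The treating physician checks eligibility before profiling (Patient selection and procedures), so a literal reading stops the patient before the tumour board sees the case. Seventeen hospitals take part, and the section on treatment at local hospitals says that many of them have little experience of running trials. One site could refuse a patient whom another would enrol. Refusal works against the second primary objective, which is patient access. Enrolment leaves a patient on study who does not meet the printed criterion.

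**Working it through.** The point depends on no sample size or rate, so the check is a comparison of texts.

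**Step 1: scope of the exclusion.** The exclusion sentence names no disease group. The same section does limit RECIST to solid tumours, so the authors set a limit where they wanted one. The exceptions are two named markers in two named cancers, and the wording does not present them as examples.

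**Step 2: apply both parts of the criterion to typical cases.** These cases are illustrations. The article does not say how often each occurs.

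| Case | Scale named? | Passes the exclusion sentence as printed? |
|---|---|---|
| Solid tumour with measurable lesion | Yes (RECIST) | Yes |
| Prostate cancer, PSA only | Exception stated | Yes |
| Lymphoma with imageable nodes | Yes (Lugano) | Yes |
| Myeloma with a measurable plasmacytoma | Yes (IMWG) | Yes |
| Myeloma followed only by serum or urine protein or marrow | Yes (IMWG) | **No** |
| AML with a measurable extramedullary lesion | Yes (ELN-AML) | Yes |
| AML assessed only in marrow or blood | Yes (ELN-AML) | **No** |

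The conflict is confined to the two rows marked No. In both, the criterion supplies a response scale and then refuses entry.

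**Step 3: is exclusion the intent?** Haematology units recruit, the tumour board includes haematology, and the organ-function criterion refers to haematological diagnoses. Together with the named scales, this makes deliberate exclusion implausible. The fault lies in the wording.

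**Step 4: does later text repair it?** The treatment-phase section requires the screening criteria as well as its own. It says that drug-specific criteria may be added, which does not suggest that they relax the earlier ones. No printed section lifts the restriction.

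**Step 5: side check of the operating characteristics.** The rule under Statistical analyses is to stop at 0 of 8 and otherwise to call the cohort positive at 5 or more of 24. With X ~ Bin(8, p) and Y ~ Bin(16, p),

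P(positive) = Σ (x = 1 to 8) P(X = x) · P(Y ≥ 5 − x).

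- p = 0.10 gives 0.0778 (stated 7.8%).
- p = 0.30 gives 0.857 (stated 85%).

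Both agree with the article, and neither depends on the eligibility wording.

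**The case against.** The strongest reply is that nobody reading the criterion as a whole would conclude that it names an AML scale in order to bar AML. It opens by admitting evaluable as well as measurable disease, and the serum-marker example and the CA-125 and PSA exceptions all belong to solid tumours. The tumour board reviews profiles, and the National Principal Investigator approves new cohorts, so treatment entry does not rest on one site's literal reading. The article prints only selected criteria and visibly shortens the haematology detail, and drug-specific manuals hold more. The full protocol may word or nest the sentence differently.

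Much of this stands. It makes the contextual reading the likelier intent and lowers the severity. It does not remove the conflict. The point is not that something was left out: the sentence is printed with its exceptions, directly after the text that it contradicts. The physician's eligibility check also comes before the tumour board's review.

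A reader might infer more than the documents support:

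- **That most myeloma patients, or all AML patients, are barred.** The article gives no such share, and a patient of either kind with a measurable lesion would pass.
- **That accrual falls by some stated amount.** Any figure would only restate an assumption about how many sites read the rule literally.
- **That the stated alpha and power fail.** They reproduce, and the wording does not bear on them.
- **That the two-stage verdict would describe the wrong population whatever sites do.** If sites follow the named scales, the cohort holds the intended patients and only a formal eligibility mismatch remains.

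**Conclusion.** The concern holds as a minor contradiction in wording. Followed exactly, the printed criterion refuses AML assessed only in marrow or blood, and myeloma without disease measurable by examination or imaging. The same criterion provides response scales for both diseases, and the rest of the article shows that haematology patients are intended. The restriction carries into the treatment phase.

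The number of patients affected cannot be stated. The article gives no share, which could lie anywhere from a few patients to nearly all of those with these two diseases, and it names no AML or myeloma cohort. Patients with solid tumours, and lymphoma patients with disease that can be examined or imaged, are not touched by this conflict.

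The conclusion rests on two assumptions: that patients of the two barred kinds present for screening, and that the full protocol carries the sentence with the same scope as the article.

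**What to change.** First check the sentence in the full protocol. If it reads as printed here, reconcile it with the scales named before it in one of two ways:

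1. Limit the requirement for measurement by examination or imaging to diseases scored on lesion-based scales (RECIST, iRECIST, RANO, Lugano). Myeloma and AML then fall under the general requirement of measurable or evaluable disease, judged on their own scale.
2. Keep the sentence general and extend its exceptions to disease measurable by the IMWG or ELN-AML criteria that the section already names.

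Either gives sites one rule, and the sponsor should choose the one that matches its intent. The treatment-phase section imports the screening criteria, so it needs no second edit. The cost is one sentence at the next amendment, with no extra patients, procedures or staff and no change to the two-stage design.

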### National molecular tumour board and treatment plan

A national molecular tumour board is established as part of the public health care system and evaluate patients where comprehensive genomic profiling has been performed. They consider each molecular profile and the potential benefit of treatment with a matched drug. The national molecular tumour board is organized as a virtual meeting using a secure platform and is staffed by regular and ad hoc members nationwide, including experts in several fields, such as clinical oncology, haematology, gynaecological oncology, pathology, medical genetics, cancer biology, bioinformatics, and pharmacology. The treating physician will participate, in addition to health personnel at the relevant sites. Clinical patient characteristics presented by the treating physician include age, sex, performance status and relevant medical history. As beforementioned, possible outcomes of the review may be a proposal of treatment in a cohort in the IMPRESS-Norway study, recommendation for a different clinical study, or no available clinical studies and referral to standard treatment and follow-up. New study cohorts in IMPRESS-Norway depend on approval by the National Principal Investigator. The treatment recommendation is entered in the study database.

### Recruitment and consent

Patients will be recruited by the participating 17 hospital trusts. Prior to obtaining informed consent for molecular screening, the patient will be provided with information about molecular testing and evaluation by the national molecular tumour board (Patient Information Sheet for pre-inclusion testing—Molecular Profiling ICF). Patients found eligible for the treatment will be provided with written information on specific study drug and cohort (Patient Information Sheet for a specific clinical cohort in the trial—Drug ICF) before obtaining the second consent for entering treatment phase of the trial. The written informed consent (voluntarily) is obtained prior to any study specific procedures, including specific screening procedures. Patients have the right to withdraw from the study at any time, without giving an explanation and without consequences for subsequent care.

All patients also consent to collection of patient-reported outcome measurements (PROMS) and to coupling with data from Norwegian health registers (Cancer Registry of Norway, Norwegian Patient Registry, Norwegian Prescription Database, Primary care patient- and user Register (KPR) and Statistics Norway for socioeconomic characteristics).

### Suspected germline alteration

If the molecular analysis indicates a germ line alteration as defined by ESMO guidelines and the patient might benefit from genetic counselling, the patient can choose to be referred to a medical geneticist for such counselling. This is outlined in the patient informed consent form [28].

### Treatment at local hospitals

Patients will be treated at their local hospital, with 17 hospitals participating. The schedule of study activities is shown in Table 1 (molecular profiling) and Table 2 (treatment phase). Only HTA-approved drugs are provided, and typical toxicities will be recognised and manageable at hospitals that usually treat cancer patients. However, as many of these hospitals lack expertise in running clinical studies, and the university hospitals will provide guidance and assistance for study personnel, if needed. Children are currently not included in treatment cohorts.

**Table 1 Tab1:** Schedule of Activities (SoA) for molecular profiling

Study procedures	Molecular profiling D1	W16^a^	Survival FU
Informed consent for molecular profiling	X		
Check inclusion criteria and exclusion criteria for molecular profiling	X		
ECOG PS	X		
Survival^a^	X	X	Through cancer registry
QoL^a^	X	X	
Central lab sampling	X		
Tumor biopsy	X		
Plasma /serum samples	X		

^a^Patients not enrolled in the treatment phase are followed-up W16 for survival and QoL

**Table 2 Tab2:** Schedule of Activities (SoA) for patients enrolled in treatment-cohort

Study procedures	Screening Treatment cohort	Treatment phase						EOT	Survival FU
	(D 1–21)	D1^g^	W8^g^	W16^g^	W26^g^	W39^h^	QW13^h^		Q26W for 2 years after end of treatment
Check inclusion criteria and exclusion criteria for treatment phase + Drug specific selection criteria	X								
Informed consent^a^	X								
Medical history	X								
Drug dispensing^b^		X	X	X	X	X	X		
Physical examination	X		X	X	X	X	X	X	
Vital signs and ECOG PS	X	X	X	X	X	X	X	X	
ECG	X								
AE/SAE assessment	X		X	X	X	X	X	X	
Concomitant medication	X		X	X	X	X	X	X	
QoL (V)	X			X	X	X	X	X	
Laboratory Assessments^c^	X		X	X	X	X	X	X	
Pregnancy test^d, e^	X	Monthly as long as use of contraception is required, see drug specific amendment							
Central lab sampling	X								
Plasma/serum samples	X		X	X	X	X	X	X	
Urine^i^	X		X					X	
Feces^i^	X		X						
Tumor biopsy	X			X				X	
Other material^f^	X		X	X				X	
Tumor assessment	X		X	X	X	X	X	X	
Survival follow-up									X

^a^Drug specific informed consent

^b^Treatment according to drug specific manuals

^c^Patients should be routinely monitored for serum creatinine and electrolytes (including magnesium) while on therapy. Liver function (including AST and ALT) should be monitored monthly during the first 6 months of treatment, and as clinically indicated thereafter.

^d^Less than 72 h before treatment

^e^If patient is sexual abstinent, there is no need for pregnancy testing, but the patient must confirm abstinence monthly

^f^Pleural, effusion/ascites collected when possible/available

^g^Visit window +/− 7 days, year 1.

^h^Visit window +/− 14 days after year 1.

^i^Selected cohorts only

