The IMPRESS-Norway study design is based on the DRUP trial (Drug Rediscovery Protocol) which has been ongoing in the Netherlands for five years [17]. They treat patients with targeted drugs based on a molecular profile, and outside of their current market authorisation. The initial results from the DRUP-trial reveal a clinical benefit of 34% in the first 215 patients beyond 16 weeks [17, 18]. According to the study report, 46% of the patients that were referred after local genomic testing were included in the trial. Both the reported inclusion rate and overall rate of clinical benefit were higher than other studies of tumour molecular profiling with matched targeted treatment [8, 19]. Based on the success of the DRUP-trial, similar studies have been initiated in other European countries including Denmark, Norway, Sweden, and Finland [20].

There is a lack of data on drug safety and efficacy for rare indications outside of the approved label for many cancer drugs. Through this clinical study, where key clinical outcomes are systematically collected, missing data will be provided, and also benefit some patients by offering a new treatment line based on molecular profiling.

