## Collateral research

### Sample collection/biobanking

The collection of biological samples for translational and biomarker research is an important part of this study. Tumour samples will be collected up to at three different time points (prior to treatment, during treatment (at 16 weeks) and upon progression if not progression at or before 16 weeks). Plasma samples will be collected at evaluation timepoints, and pleura effusion/ascites will be collected if available.

Whole genome sequencing and RNA-sequencing will be performed on tumour material from before treatment, after 16 weeks (if on treatment) of treatment and upon progression. This might inform on mechanisms of response or resistance. As a part of the molecular profiling, ctDNA analyses will be performed for the first 500 patients by FoundationOne® Liquid CDx provided by Foundation Medicine Inc. This will allow for comparison between liquid biopsy and tumour biopsy. In addition, Foundation Medicine provides tests for 150 patients lacking available tumour material. For the subsequent 500 patients included in IMPRESS-Norway, ctDNA analyses will be performed inhouse and provided by Illumina (TSO500 ctDNA test). The biologic material will be stored in the IMPRESS-Norway-biobank and the data will be stored in TSD (Services for Sensitive Data). In addition, several analyses will be done on material from the different cohorts.

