### Health economics, cost-effectiveness analyses (CEA) and national registries

Health Economics data, associated with medical encounters, will be collected by the investigator and study-site personnel for all participants (both participants in a cohort and those not included in a treatment cohort) throughout the study. In addition, clinical data will be supplemented by information from several registers: Cancer Registry of Norway, Norwegian Patient Registry, Norwegian Prescription Database, Primary care patient- and user Register (KPR) and Statistics Norway for socioeconomic characteristics. Protocol-mandated procedures, tests, and encounters are excluded. Health economics research will go on throughout the duration of the IMPRESS trial and will be coordinated with the more general discussion on novel implementation methods for Precision Cancer Medicine (PCM), health technology assessments (HTA) of PCMs and data structure.

From the perspective of the Norwegian health care system, several analyses will be performed. To conduct cost-effectiveness analyses, costs and health outcomes of target drug treatment will be compared to the patient group eligible for genetic testing, but where no relevant target agents are identified. During the first years of IMPRESS-Norway, the comparator will contain an aggregated group of patients with several indications, but this group will gradually be refined to match the treated patients (for instance by indication, other condition specific characteristics, sex and age).

Costs will include costs related to genetic testing (testing, device, analysis, tumour board etc.), treatment, adverse events, follow-up and additional treatment (specialist and primary care), primary care (practical assistance and institutions), and best supportive care.

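### Treated patients who stop before week 16 have no scheduled quality-of-life measurement at week 16 or after end of treatment, whereas untreated patients are measured at week 16

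*Protocol article*

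**What the plan says.** The two schedules are in the protocol article under Treatment at local hospitals.

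- **Untreated patients (Table 1).** QoL is marked at day 1 of molecular profiling and at week 16. The footnote reads "Patients not enrolled in the treatment phase are followed-up W16 for survival and QoL". It sets no condition on disease course or later care. After week 16 there is only survival, taken from the cancer registry.
- **Treated patients (Table 2, "Schedule of Activities (SoA) for patients enrolled in treatment-cohort").** QoL is marked at screening, W16, W26, W39, every 13 weeks thereafter, and EOT. It is not marked at D1 or W8. The W16 column stands under the treatment-phase heading, and drug dispensing is marked at the same visit. The column after EOT, "Q26W for 2 years after end of treatment", has one row marked: survival.

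The section on health economics plans a comparison of these two groups: "costs and health outcomes of target drug treatment will be compared to the patient group eligible for genetic testing", limited to those in whom no relevant agent was found. Study objectives lists patient-reported outcomes and cost-effectiveness as exploratory.

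**The concern.** The groups that are to be compared are not measured under the same rule. For the untreated group, week 16 is the only QoL value after baseline, so it is the natural common time point. At that point an untreated patient who is alive is due a questionnaire whatever has happened since. A treated patient is due one only if still in the treatment phase.

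Treated patients who are missing at week 16 are missing because they stopped, which in this setting will mostly mean progression or toxicity. The treated values that remain are likely to be better than the treated group as a whole.

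At stake is the QoL part of an exploratory comparison. No cohort decision, primary endpoint or safety conclusion depends on it. The gap is nonetheless one of data collection: an analysis plan can choose an imputation, but it cannot recover questionnaires that were never sent.

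**Working it through.** The article gives no expected QoL completion rate, so there is no figure of its own to reproduce. The nearest is an external result in Background, "The initial results from the DRUP-trial reveal a clinical benefit of 34% in the first 215 patients beyond 16 weeks", that is 0.34 × 215 = 73.1, about 73 patients. It is a benefit rate in another trial and serves here only as a plausible level of disease control.

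**Step 1. Coverage by type of patient, read from the tables**

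| Patient | Baseline QoL | QoL at week 16 | Other QoL after baseline |
|---|---|---|---|
| Untreated, alive at week 16 | yes | yes | none |
| Treated, still on treatment at W16 | yes | yes | later visits, EOT |
| Treated, stopped before W16 | yes | none scheduled | EOT only |

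**Step 2. Share of treated patients who reach the W16 visit**

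Tumour assessment is scheduled at W8 and W16. Assume exponential time to progression and stopping only when a scheduled scan shows progression. Everyone progression-free at W8 then reaches the W16 visit, including those whose progression is first seen there. If c is the disease control rate at W16, the share reaching the visit is s = √c.

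- c = 0.34: s = √0.34 = 0.583, so 0.417 stop earlier.
- c = 0.30 (the rate of interest in Statistical analyses): s = 0.548, so 0.452 stop earlier.
- Range c = 0.10 to 0.50: s = 0.316 to 0.707, so 0.684 to 0.293 stop earlier.

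**Step 3. Overstatement of the treated mean if only W16 values are used**

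Let d be the fall in utility off treatment. The article gives no utilities; d = 0.10 to 0.20 is an assumption. The observed mean is the on-treatment value u, and the mean over all treated patients is u − (1 − s)d. The overstatement is therefore (1 − s)d, whatever u is.

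- c = 0.34: 0.417 × 0.10 = 0.042 to 0.417 × 0.20 = 0.083.
- c = 0.30: 0.452 × 0.10 = 0.045 to 0.452 × 0.20 = 0.090.
- c = 0.10: 0.684 × 0.10 = 0.068 to 0.684 × 0.20 = 0.137.
- c = 0.50: 0.293 × 0.10 = 0.029 to 0.293 × 0.20 = 0.059.

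**Step 4. The same with EOT values carried forward**

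If QoL at EOT has already fallen by d, the overstatement is 0. If it has fallen by only half of d, half remains: at c = 0.34, 0.417 × 0.05 = 0.021 to 0.417 × 0.10 = 0.042.

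The calculation leaves out deaths before week 16, and stopping between scans for toxicity, which would lower s.

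**The case against.** A reader might infer something stronger: that the treated group's QoL, and any QALYs built on it, come only from its best third. On that reading the overstatement is 0.66 × 0.10 = 0.07 to 0.66 × 0.20 = 0.13. The document does not support this, for four reasons.

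- QoL is marked at EOT. Early stoppers who attend that visit contribute a value when they stop, so they are not absent from the post-baseline data.
- The 34% is another trial's benefit rate and not W16 attendance in this one. Under the assumptions of Step 2, patients found to be progressing at W16 also complete that visit: (0.583 − 0.34)/0.583 = 42% of those attending. The W16 respondents are then not purely the patients with disease control.
- QALYs are not named. The article says that health outcomes will be compared but not that W16 QoL will be, and the method may be in the full protocol or analysis plan, which are not shown.
- Untreated values also come only from patients alive and able to answer. The clocks differ as well: Table 1 counts from molecular profiling, whereas Table 2 has a separate screening period and its own D1. The direction of bias is probable for a W16 comparison, but not proven for whatever analysis is planned.

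It can also be said that the link between W16 QoL and being on treatment is read from the column heading. The explicit condition, "after 16 weeks (if on treatment) of treatment and upon progression", is written for tumour sequencing and not for QoL. That is fair. If the sponsor means W16 QoL to be collected regardless of treatment status, Table 2 should say so, and the same footnote does it.

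What survives is the difference between the schedules. An EOT value is taken at a variable, earlier time and says nothing about QoL afterwards.

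**Conclusion.** The point holds in a limited form. Treated patients who stop before week 16 have QoL at screening and EOT but none scheduled at week 16 or later, while untreated patients have it at week 16. A treated-versus-untreated comparison at that time would rest on treated patients still on treatment and would probably favour treatment.

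The illustrative size is an overstatement of the treated mean of about 0.04 to 0.08. It falls to between 0 and about 0.04 if EOT values are carried forward and QoL at EOT has already dropped at least half way. These figures rest on 34% control at W16, exponential progression, stopping only at scheduled scans, and an assumed utility loss of 0.10 to 0.20. Severity is low, because both objectives concerned are exploratory.

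**What to change.** Add a footnote to the QoL row of Table 2: the W16 questionnaire goes to every patient who started treatment and is alive, on or off drug. Use that set in any treated-versus-untreated QoL comparison.

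The cost is one footnote and one questionnaire to patients who stopped early. According to Recruitment and consent, all patients already agree to the collection of patient-reported outcomes. Nothing in treatment or clinical management changes. The downside is some non-response after stopping, so completion should be reported separately for patients on and off treatment. The footnote does not remove the difference in time origin between the two tables, which should be kept in mind when the results are read.
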